### Randomisation

Randomisation will be performed using the Stata 16.0 random number generator (College Station, TX, United States).

### Data Management

The target population will extract thanks to a query in the CRCDC-Pays de la Loire’s business software called Zeus d’Osi-Santé. The list of patients will be included first and last names, dates of birth, addresses, and social security numbers to avoid confusion and duplications. Results of HPV self-sampling test and questionnaire data will be compiled in a restricted access file. The CRCDC will ensure the completeness of data collection for women who have visited their physician/midwife for gynaecological sampling through the collection of reimbursement data and screening test results from cytopathology or medical laboratories.

The interviews and focus groups are digitally recorded after information about the purposes of the research and the completion of a consent form.

### Statistical Methods

The Unit of Cancer Epidemiology (Sciensano, Brussels, Belgium) will perform the statistical analyses of a pseudo-anonymised data file containing records of participating women.

Contrasts in response in women included in the self-sampling arms versus the control arm will be evaluated as relative participation (proportion participating in one arm/proportion participating in another arm) and participation differences (proportion participating in one arm - proportion participating in another arm). A positive response is defined as a woman who has received a screening test: a cervical smear (in the control arm) and a vaginal or urine self-sampling (experimental arm) within 6 months after the offered intervention. The cumulative response rate over time (total number of responses observed by time of observation) will be assessed graphically using Kaplan-Meier curves. Reaching a plateau will indicate that the “invitation effect” is ending and this information will help to define the observation period required to observe the effect of an intervention in the future. Inter-arm contrasts in cumulative participation will be evaluated by Cox’ proportional hazard regression.

Two types of analysis will be performed: per protocol analysis where only responses foreseen in the respective arm will be considered, whereas in the intention to treat analysis also women that are screened not according to the foreseen intervention will be considered as well (also those performed on samples taken by a clinician in the self-sampling arms). The influence of age category and geographical area will be assessed using by Pearson’s *χ*
^2^ statistic and logistic regression.

In addition, knowledge, attitudes, opinions and experiences of participating women, as well as the variation by age, geographical area (including the deprivation index corresponding with the statistical sector where the woman is domiciled) and previous screening history will be assessed in the returned questionnaires.

All statistical analyses will be performed using Stata version 16 (StataCorp LLC, College Station TX, United States). The *p*-value for statistical significance will be defined at ≤0.05.

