### Outcomes

#### Primary Outcomes

Participation rates (number of responding/number of invited) in each arm, difference and ratios of participation rates between the control and the two intervention arms.

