#### Secondary Outcomes

⁃ Contrast in participation between the 2 experimental arms and between women that received a questionnaire or not.⁃ Screen test positivity rates (presence of high-risk HPV and distribution by HPV type and/or of abnormal cytology) in the respective arms and contrasts between arms.⁃ Adherence to follow-up of screen-positive women and contrasts between arms.⁃ Impact of covariates on the participation and adherence to follow-up (age, reimbursement status, geographical area).⁃ The obstacles and levers emerging from the speech of the women and health professionals participating in the research will be analysed on the basis of a thematic analysis [21] integrating a specific focus on the indicators identified in previous studies (e.g., lack of time, discomfort with regard to the location or bad experience encountered during another type of examination, etc.). This study will be doubled by a categorical analysis based on Linguistic Inquiry and Word count which allows, among other things, to automatically categorise positive or negative emotions related to themes for example associated with the disease or beliefs [22].

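### The crude arm contrasts are valid, but reporting standardised differences and ratios from the logistic model already planned would add a little precision and put covariate effects on the primary scale

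*Protocol article*

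**What the plan says.** Primary Outcomes sets the measures as participation rates per arm with "difference and ratios of participation rates between the control and the two intervention arms". Statistical Methods carries this through: the contrasts "will be evaluated as relative participation (proportion participating in one arm/proportion participating in another arm) and participation differences", each defined directly from the two arms' proportions. No covariate is mentioned there.

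Covariates have their own sentence in the same section. It begins "The influence of age category and geographical area will be assessed using by" and goes on to name Pearson's chi-square and logistic regression. It does not say whether arm is in that model or on what scale results will be reported. Secondary Outcomes lists this work as "Impact of covariates on the participation and adherence to follow-up (age, reimbursement status, geographical area". For time to response, "Inter-arm contrasts in cumulative participation will be evaluated by Cox’ proportional hazard regression", again without covariates.

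Data Management lists "first and last names, dates of birth, addresses, and social security numbers" for the target population. The Randomisation section says only "Randomisation will be performed using the Stata 16.0 random number generator" and names no stratification factor.

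**The concern.** Two things follow from keeping the arm contrasts and the covariates apart.

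- **Precision.** Age (from date of birth) and department (from address) are held for every invited woman before mailing. Using them in the arm contrast, with the difference and ratio kept as estimands, removes chance imbalance and narrows intervals. As written, that gain is not used. It matters least for kit versus control, and somewhat more for urine versus vaginal, where the true difference may be small.
- **Scale.** If the logistic results are reported in their default form, odds ratios for age and area will stand beside participation ratios and differences for the arms. An odds ratio lies further from 1 than the corresponding ratio, and the gap widens when the outcome is common, as adherence to follow-up is expected to be. The scale also affects consistency across areas, which Objectives names as an aim: a constant absolute gain is not a constant odds ratio.

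**Working it through.** **1. The plan's own figure.** Sample Size gives 588 to 3,123 women per arm (control 12–14%, experimental 3–7 points higher, 95% confidence, 90% power). I used the two-sided formula for two crude proportions with pooled variance and continuity correction. Here p̄ is the mean of the two rates and d their difference:

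n = [1.96·√(2p̄(1−p̄)) + 1.2816·√(p0(1−p0)+p1(1−p1))]² / d², then n_cc = (n/4)·[1+√(1+4/(n·d))]².

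- 12% vs 19%: n = 560, corrected 588.
- 14% vs 17%: n = 3,057, corrected 3,123.

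Both are reproduced exactly. The planned 5,000 per arm exceeds both.

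**2. Crude precision at 5,000 per arm, 12% vs 15%.** SE = √[(0.12×0.88 + 0.15×0.85)/5,000] = 0.00683. The 95% half-width is 1.96 × 0.00683 = 1.34 points, and power is Φ(0.03/0.00683 − 1.96) = 99.25%. For 14% vs 17%, power is 98.6%.

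**3. Gain from adjustment: one three-level predictor.** The article gives no covariate strengths, so the spreads below are assumptions, all with mean 16%. R² = variance of the group rates / [0.16 × 0.84]. Equivalent extra women per arm = 5,000 × [1/(1−R²) − 1]. Interval narrowing = 1 − √(1−R²).

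| Rates across thirds | R² | Extra women per arm | Interval narrower by |
|---|---|---|---|
| 13/16/19% | 0.45% | 22 | 0.2% |
| 10/16/22% | 1.8% | 91 | 0.9% |
| 8/15/25% | 3.6% | 188 | 1.8% |

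**4. Gain from adjustment: age and department together.** This check uses four equal age groups (assumed) by three departments, weighted by the populations in Study Setting (67,946; 126,765; 157,050). Covariate strengths are again assumed. The contrast is 12% vs 15%, standardised over the 12 cells.

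| Control rate across cells | Variance cut | SE | Power at 5,000 | Power at 3,123 |
|---|---|---|---|---|
| none (crude) | – | 0.00683 | 99.25% | 93.48% |
| 9% to 14% | 0.2% | 0.00682 | 99.26% | 93.53% |
| 7% to 18% | 1.1% | 0.00679 | 99.30% | 93.73% |
| 3% to 25% | 4.3% | 0.00668 | 99.43% | 94.41% |

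Interval narrowing in the strongest case is 1 − 0.00668/0.00683 ≈ 2.2%. The power gain at the planned size is at most 99.43 − 99.25 = 0.18 points.

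**5. Odds ratio against ratio.** OR = [p1/(1−p1)]/[p0/(1−p0)]; RR = p1/p0.

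| Pair | RR | OR |
|---|---|---|
| 12% vs 15% | 1.25 | 1.29 |
| 12% vs 19% | 1.58 | 1.72 |
| 14% vs 21% | 1.50 | 1.63 |
| 15% vs 22.5% (a covariate, assumed) | 1.50 | 1.65 |
| 80% vs 92% adherence (80% assumed; 92% is the upper rate in Sample Size) | 1.15 | 2.88 |

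For consistency across areas, a constant gain of 3 points is an OR of 1.50 at a control rate of 6.6% (6.6% vs 9.6%) but 1.21 at 18.2% (18.2% vs 21.2%).

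**The case against.** The strongest reply is that nothing here is wrong. In a 1:1:1 randomised trial a ratio or difference of raw proportions is unbiased and matches the stated primary outcome. No stratification factor is stated, so the design does not oblige adjustment. With 5,000 per arm, chance imbalance is small and already covered by the ordinary interval: a one-third department share differs between two arms with SE √(2 × ⅓ × ⅔ / 5,000) ≈ 0.9 points. All of this stands.

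It is also fair to say that the article neither excludes adjusted estimates nor announces odds ratios, and that such detail is commonly left to an analysis plan. That stands too, and it is why the point concerns only the default output of a named method. The arm pairs in step 5 show how far the scales diverge; they are not results that the plan would report as odds ratios. Logistic regression is named for age category and area, and its use for adherence is not explicit, so the adherence example applies only if adherence is modelled the same way.

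A reader might infer that covariate effects cannot be set against the trial's ratios and differences at all. The documents do not support that. A logistic model that includes arm yields standardised ratios and differences after fitting, and tabulated participation by age and area can be read directly on the primary scale. A reader might also infer that every useful covariate is already in hand. The deprivation index is not on the extraction list. Statistical Methods mentions it only for returned questionnaires, and it would need address linkage.

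**Conclusion.** This holds as a minor improvement in efficiency and consistency of scale. The primary contrasts are valid, and no conclusion of the trial is at risk. A reader might infer that the unadjusted analysis biases the result or leaves the trial short of power. Randomisation and about 99% power for kit versus control rule out both.

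The precision left unused is small: intervals roughly 0.2% to 2% narrower, and 0.2 power points or less at 5,000 per arm. Those figures rest wholly on assumed covariate strengths. The scale difference is slight for small effects at low rates (1.25 against 1.29), moderate at the upper end of the assumed effects (1.58 against 1.72), and large only for a common outcome such as adherence. The case for acting is that the change costs little and loses nothing, since the estimands stay the same and the crude figures remain on view.

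**What to change.** For participation among all randomised women, state that the planned logistic model will include arm, questionnaire allocation, age and department. Report marginally standardised participation differences and ratios with 95% confidence intervals (Stata margins), with the crude figures alongside. Report covariate effects on participation as standardised differences and ratios, and not as odds ratios only. If adherence is modelled the same way, do likewise there, in a separate and simpler model restricted to screen-positive women, because that group is much smaller.

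Keep the deprivation index optional, since it needs linkage from addresses for all invited women.

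The cost is a sentence or two of analysis text and a few lines of code in software already planned. No new data collection is needed for age and department. One practical check: Statistical Methods describes the analysis file as holding records of participating women, so confirm that it carries age and department for non-responders too. The covariate analysis already planned needs them in any case.

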### Additional Analyses

#### Laboratory Testing and Gynaecological Follow-Up

The vaginal and urinary self-samples will be analysed at the virology laboratory of the Angers University Hospital using real-time PCR for the search of oncogenic HPV with extended genotyping (BD Onclarity™ HPV test, BD Diagnostics, Burlington, NC). The BD Onclarity™ HPV test provides results for six individual high-risk HPV genotypes (16, 18, 31, 45, 51 and 52), with the remaining eight high-risk genotypes reported in three small groups: (33, 58), (35, 39, 68) and (56, 59, 66). The Onclarity™ assay fulfills requirements for HPV tests in the context of cervical cancer screening [24, 25]. Negative results will be sent to the woman, her GP and the CRCDC. Positive results with oncogenic HPV will be sent to the GP and the CRCDC. The woman will receive a letter urging her to go to her GP to get her result. The CRCDC will follow up with the doctor and the woman if she had not had a smear after 6 months. Reminders will be regularly until the follow-up examination is carried out.

#### Attitudes and Acceptance by Women

A questionnaire will be sent to half of the population of the three arms to assess the reasons for not performing a cervical smear. The benefits of performing self-sampling will concern arms 2 and 3 with the self-samplings kits (see Supplementary Material).

Then, in order to understand the obstacles of the target population regarding screening, semi-structured interviews will be first conducted by psychologists [26, 27]. The interviews will be recruited among the women who performed the self-sampling and who have agreed to leave their contact information. A random draw based on socio-demographic and territorial characteristics will then be carried out to avoid the over-representation of certain populations. Special attention will be paid to the population characterised as under-screened (over 50 years old) and to vulnerable populations (economic precariousness because they benefit from complementary health care, medically desertified places, etc.). These interviews may be conducted face-to-face or remotely depending on the woman’s medical and geographical situation. The objective will be to determine the motivations of the woman who returned a self-sample, stopping on the cognitive path from the knowledge of the device to the pre-diagnosis and its consequences but also what they do with the result received. Indeed, the reception of a negative, unsatisfactory or positive result may not lead to a medical consultation, even though it would be recommended. The semi-directive interview will also allow gathering the experience of the sample collection process to measure satisfaction and assess the value given to the information received.

After the first series of exploratory semi-structured interviews (envisaged number of interviews: 6), focus groups discussions will be implemented. According to Kitzinger and al. [28, 29], focus groups will bring together between five to eight participants and, according to Hennink et al. [30], their number will be between 6 and 8. The use of focus groups is particularly useful in understanding similarities and differences in the thoughts, views and emotions of participants [31]. This method is therefore indicated for the purpose of the study and allows the obtaining of additional information for semi-structured interviews. This qualitative technique has been chosen in numerous recent studies relating to self-sampling and cervical cancer [32–34]. Its use will give the possibility of international comparisons. Third, these focus groups will be followed by a new series of semi-structured interviews to investigate elements that emerge from the focus groups and require individual exploration. Raising the number of interviews to 10–14, this series will ensure that data saturation is achieved.

#### Attitude of Health Professionals

In order to identify the obstacles and levers of primary care health professionals (GPs, midwives and gynaecologists), psychologists will organise semi-structured interviews, depending on the professional and territorial constraints of the surveys, in particular to take into account the importance of recruiting professionals practicing in rural or semi-rural areas.

The health professionals will be informed in advance by mail of the conditions of the research and will be offered to participate in an interview. They will be informed that they will be contacted by telephone after the letter has been sent in order to allow for a further exchange of information and to agree, if they wish, on the conditions for the implementation of this interview. The aim of these semi-structured interviews will be to understand the different situations encountered, the resources mobilized, the difficulties overcome and those remaining to improve both the system and the modalities (sending the screening kit at home or to the doctor’s office), based on collective exchanges. The interviews will be conducted in the number necessary to reach saturation of responses [35].

Semi-structured interviews and focus groups will be recorded and transcribed. They will be analysed using conventional qualitative content analysis [36].

### Ethical Consideration

The CapU4 study protocol received approval from the French “Sud-Est I Ethics Committee” (2021-123, November 25, 2021, France). The supply and use of these records for the programme have been submitted to the Commission Nationale de l’Informatique et des Libertés, French National Data Protection Authority in September 2021 (ref. 2223607v0). Women’s return of the vaginal and urinary self-samples will constitute consent for HPV testing. Written informed consent to the audio recording of the interviews and anonymised digital transcripts will be obtained from the women who will participate in the individual semi-structured interviews and/or focus groups.

## Discussion

CapU4 will for the first time compare directly two experimental invitational strategies (including self-sampling of vaginal specimens and collection of first-void urine) with the current procedure including traditional reminder letters with the aim to increase participation in cervical cancer screening. The trial will take place in three rural medically under-served departments, in France, with low screening coverage.

Based on the results of the CapU3 study, we expect that the participation in the self-sampling arms will be between 15% and 20% [20] which should be higher than the response to a routine reminder letter inviting to contact a health professional for the collection of a cervical smear. A recent meta-analysis has shown that strategies including sending self-sampling kits to the women’s home address are more effective than “opt-in” strategies where women have to request a self-sampling kit or routine letters inviting women to have a cervical specimen by a clinician [14]. Another French study also demonstrates that offering a return-mail kit for in-home vaginal self-sampling is more effective and cost-effective than a recall letter in increasing participation in cervical cancer screening [23].

Self-sampling is becoming increasingly important and applicable to supplement organised screening programme. Vaginal self-sampling modalities are recognised in France and recommended for non-participating women since 2019 [10].

Several studies have been set up recently that compares the clinical accuracy of HPV testing on diverse types of self-samples (vaginal, first-void urine) with HPV testing on cervical samples taken by a clinician [16, 37–39].

The areas of the three departments of Sarthe, Mayenne and Vendée are for the most part in the area of medical priority intervention. The healthcare context linked to the COVID-19 pandemic, with three periods of confinement, exacerbates inequalities in access to care with an increase in territorial inequalities due to transport restrictions. The option to collect a self-sample at home may address this accessibility problem. Home-based sample collection should be done in accordance with national recommendations and as part of an organised screening programme that ensures the follow-up of screen-positive women. We will be able to assess accessibility to health services by correlating participation with the density of health services corresponding with the statistical sector.

CapU4 will also monitor the follow-up of screen-positive women in each of the arms through the regional screening centre (CRCDC), with particular attention to the adherence of to the recommendation to have a cervical smear to triage women with an HPV-positive self-sample. The CapU3 study had enabled more than 92% of the women screened to have gynaecological follow-up [20]. The same result is expected in this study.

Strategies that overcome barriers to women’s participation are imperative to improve coverage of cervical screening programmes, but these new strategies also need to be evaluated. The knowledge of obstacles to CC screening will make it possible to optimise the modalities (instructions for use, receipt of results mail) measuring women’s satisfaction. Templates from other countries or regions and suggestions captured from focus-group discussions could help to adapt communication strategies and improve the participation rate of the target population.

This analysis will make it possible to refine the instructions for use and access methods for self-sampling for deployment to all follow-up campaigns in the region and even nationally.

The CapU4 will be completed with an economic analysis where we will assess the incremental cost-effectiveness (extra cost per extra screened woman in the two self-sampling arms versus control arm and in the urinary versus vaginal arms).

Finally, from the qualitative information collected in the in-depth interviews, we will be able to identify the effective strategies for reminders (by simple mail, urinary or vaginal self-sampling kits) for both professionals and the general public.
